We will test the hypothesis that relative changes in malaria mortality will be similar using the two methodologies. Point estimates of relative mortality from one year to the next will be calculated and compared, by calculating the variance of the streamlined method using the delta method and the variance of the gold standard method using a bootstrap test. Assuming that we will have a sample size of 800 children per year from the community surveys with baseline mortality rates of 6.5, 12.9, and 19.4 per 1000 (based on 2006 Uganda DHS survey and assuming malaria-attributable mortality of 20%, 40%, and 60%), and baseline number of malaria-associated deaths from our inpatient surveillance of 12, 60, and 84 (based on preliminary inpatient surveillance data) for low, medium, and high transmission sites respectively, we will have 80% power (one-sided significance level of 0.05) to reject the alternative hypothesis that there is an absolute difference in estimates of relative mortality of 1.30, 0.50 and 0.41 for low, medium, and high transmission sites, respectively. Whether or not these analyses show any evidence of significant differences between the methods, we will explore whether there is any systematic bias in the estimate of the streamlined method compared to the gold standard method (e.g. the streamlined method consistently over- or underestimates relative mortality). Log-linear regression models will be used to predict the result of the gold standard method using data from the streamlined method, allowing adjustment for bias.

Immunology. The age-dependent SCR will be determined for each study area at each time-point and related to the concurrent parasite prevalence by RDT, microscopy and PCR and anemia prevalence.

Evidence for a change in transmission intensity will be assessed by fitting more than one force of infection to age-dependent antibody prevalence data. Antibody prevalence and density in school children will be related to the concurrent parasite prevalence by RDT, microscopy and PCR and anemia prevalence.

Decision on the optimal methods for surveillance. If any of the streamlined methods described above do not approximate the corresponding gold standard methods and attempts at correcting systematic bias are not reliable (e.g. unable to consistently predict estimates using the gold standard method) then we will conclude that the streamlined method is not a reasonable substitute for the gold standard method.

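### The mortality comparison puts a bootstrap variance on a raw year-on-year ratio with about five expected baseline deaths at the low site; that variance does not exist without an ad hoc zero rule, and the raw scale makes the error rate depend on direction

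*Protocol*

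**What the plan says.** Protocol section 8.2 (Mortality) takes relative change as the primary mortality metric: "Point estimates of relative mortality from one year to the next will be calculated and compared". The inpatient (streamlined) variance comes from the delta method. The community-survey (gold standard) side uses "the variance of the gold standard method using a bootstrap test".

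The planning inputs are "a sample size of 800 children per year from the community surveys with baseline mortality rates of 6.5, 12.9, and 19.4 per 1000" for the low, medium and high sites, and "baseline number of malaria-associated deaths from our inpatient surveillance of 12, 60, and 84". From these the section claims "we will have 80% power (one-sided significance level of 0.05") for absolute differences in relative mortality of 1.30, 0.50 and 0.41. It adds that log-linear models will predict the survey result from the inpatient data.

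Three things are therefore fixed: the ratio scale, a variance obtained by resampling, and margins expressed as absolute differences between ratios. The number of resamples, the resampling unit and the handling of zero deaths are not given.

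**The concern.** The survey ratio has baseline-year deaths in its denominator. When few deaths are expected, some bootstrap resamples contain none, and the ratio in those resamples is infinite or undefined. A variance computed over such resamples has no finite limit, so the reported number depends on whatever is done with the zeros.

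A second problem is independent of the bootstrap. A ratio of small counts is skewed to the right, and its standard error grows with its value. Treating the difference of two such ratios as symmetric around its estimate makes agreement easier to declare on one side than on the other. The result feeds the decision rule at the end of section 8.2 on whether the streamlined method can replace the gold standard.

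**Working it through.** **1. Expected survey deaths.** The inputs are from section 8.2, reading 800 children per year as per site because the rates and inpatient counts are given by site.

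- Low: 800 x 6.5/1000 = 5.2
- Medium: 800 x 12.9/1000 = 10.3
- High: 800 x 19.4/1000 = 15.5

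The rates agree with their stated basis, "assuming malaria-attributable mortality of 20%, 40%, and 60" per cent: 6.5/0.20 = 32.5, 12.9/0.40 = 32.25 and 19.4/0.60 = 32.3 per 1000, a common all-cause rate.

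**2. The plan's own figures.** With delta-method variances in both arms and both ratios equal to 1, the detectable difference is (1.645 + 0.842) x sqrt(2/D + 2(1-p)/(800p)), where D is the inpatient count and p the survey rate. This gives 1.84, 1.18 and 0.96, not 1.30, 0.50 and 0.41. The protocol does not state the relative mortality it assumed, so this does not prove its figures wrong. Nothing below rests on it.

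**3. Zero-denominator resamples.** With k observed baseline deaths among 800, a resample has none with probability q = (1 - k/800)^800. For k = 5, q = (1 - 5/800)^800 = 0.66%. Resampling about 400 households a year instead gives 0.65%. Since q > 0, the ideal bootstrap variance of the ratio does not exist, whatever the number of resamples B.

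A run of B resamples contains at least one zero with probability 1 - (1 - q)^B. Averaged over k ~ Binomial(800, p):

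| Site | B = 50 | B = 100 | B = 200 | B = 500 | B = 1,000 |
|---|---|---|---|---|---|
| Low | 40% | 51% | 61% | 74% | 81% |
| Medium | 4% | 6% | 9% | 15% | 20% |
| High | 0.2% | 0.4% | 0.6% | 1.2% | 2% |

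**4. What the zero rule does.** With five deaths in each year, the bootstrap SD of the ratio is:

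- 1.11 if zero resamples are dropped
- 1.21 if 0.5 is added throughout
- 1.36 if zero is replaced by 0.5
- 4.5 if zero is replaced by 0.1
- infinite with no rule

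**5. Direction of error.** Studies were simulated (3,000 to 4,000 per scenario, 500 resamples each, zero resamples dropped). Survey deaths were binomial among 800, the delta-method variance was used for inpatient counts of 60 and 84, and the true gap was set equal to the stated margin. A one-sided z test at 1.645 should then be wrong 5% of the time. At the medium and high sites:

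- Survey ratio truly higher: roughly 6-8%
- Inpatient ratio truly higher: about 0.1% or less

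With delta-method variances in both arms the asymmetry remains (about 7-10% against 0.1-0.7%), so it comes from the raw ratio scale and not from the bootstrap.

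The scale problem also shows in the margins. If the inpatient ratio is 1, a survey ratio lower by 1.30 would be 1 - 1.30 = -0.30, which cannot occur.

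**The case against.** **Resample number and zero handling can be left to the SAP.** This stands for those details. It does not reach the core, because the protocol itself fixes a variance of a raw ratio and absolute margins, and no later detail makes that variance exist.

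**The share of affected runs rests on an assumed B.** This is correct. At B = 50 fewer than half of low-site runs are affected, and the share also falls if more deaths are observed (28% at B = 1,000 with eight deaths).

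**A reader might infer that the low-site test usually cannot be computed.** The documents do not support that. Few resamples are affected, and common rules give similar standard errors: the median at the low site is 1.08 with zeros dropped and 1.19 with 0.5 added. The very large values need unusual rules.

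**A reader might infer that the delta method is unsound for the inpatient arm.** Delta and simulated standard errors are 0.183 and 0.190 for 60 deaths, and 0.154 and 0.159 for 84. They part only at 12 deaths (0.41 and 0.54). Using different estimators for two independent sources is not itself a fault.

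**A reader might quote 15% power at the low site.** With both ratios truly 1, that is one direction only. The other gives about 36%, and both together about 8%.

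**If similarity requires excluding both bounds, the error is not inflated.** This is fair: false declaration was then at most about 2% at the medium and high sites. The 6-8% applies to a single one-sided test, and the protocol does not say which is meant.

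**More deaths may be available, and the comparison is not a listed objective.** Verbal autopsy covers five years (section 5.2.5), but the power statement uses 800 children per year. Objective 2 covers only parasitemia and anemia, and the decision rule also considers bias correction, which limits the consequence.

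**Conclusion.** The point holds as a flaw in a stated method, of moderate weight. At the low site the bootstrap variance of the ratio has no finite ideal value, and the number used would be set by an unstated rule (SD 1.11 to 1.36 under common rules with five deaths in each year). The share of runs affected is about 51% to 81% for 100 to 1,000 resamples. The problem is smaller at the medium site and slight at the high site.

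The direction-dependent error at the medium and high sites is a separate consequence of comparing skewed ratios on the raw scale. It assumes single one-sided z tests at the stated margins.

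Both conclusions rest on the protocol's 800 children per year, read as per site, and on its own baseline rates. They do not show that the test cannot be run, or that the stated detectable differences are wrong.

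**What to change.** Replace the difference of raw ratios with one Poisson (log-linear) model of malaria deaths on method, year and method-by-year, with live births as the offset for the survey arm. The interaction is the ratio of the two relative changes. Report it with a profile-likelihood or exact conditional interval, given as a one-sided bound if a year has no deaths. State the margins as ratios, and say whether similarity requires one bound or both.

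This needs no resampling, treats both sources alike and fits the log-linear models that section 8.2 already plans. Household clustering does not combine readily with an exact interval and is at most a sensitivity analysis.

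The cost is analysis wording and re-expression of 1.30, 0.50 and 0.41 as ratios; no new data are needed. The low-site interval will still be wide, since no method makes about five deaths precise.

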# 4.0 STUDY METHODS

## 4.1 Overall study design

We propose to conduct cross-sectional surveys in communities and primary schools twice a year for at least 2 years in the 3 different sites. The surveys will be timed to correspond to the high and low malaria transmission seasons, when possible. In the community surveys, 200 households will be recruited from a list randomly generated from a census database at each site. The community surveys will consist of three components: (1) a household survey targeting heads of households, (2) a women’s survey targeting all women of child-bearing age (15-49 years), and (3) clinical surveys of all children under fifteen years of age, and of one household member within the age category 15-24 years, 25-34 years, 35-44 years, 45-54 years, and > 55 years. The clinical surveys will include a fingerprick blood sample for measurement of hemoglobin, thick and thin blood smear, rapid diagnostic test (RDT) for malaria, and filter paper blood sample. The school surveys will be conducted in 3 randomly selected primary schools per site. A total of 100 randomly selected children will be recruited in each school. The school surveys will include only the clinical assessments including measurement of temperature, and a fingerprick blood sample for measurement of hemoglobin, thick and thin blood smear, RDT for malaria, and filter paper blood sample.

##

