| Population | 204700 | 387600 | 536,900 |
| Urbanization level | 6.3% | 22.1% | 6.5% |
| Number of households | 43500 | 84000 | 112,300 |
| Persons per household | 4.7 | 4.5 | 4.8 |
| Entomology (data collected 2001-2002) | | | |
| Entomologic inoculation rate | 6 | 6 | 562 |
| Predominate vector species | *An. gambiae ss* | *An.gambiae ss* | *An.gambiae ss* |
| Measures of infection (data collected in children 2-9 years of age, 1999) | | | |
| Parasite rate | 43% | 15% | 91% |
| Malaria control interventions | |  |  |
| IRS, year (% targeted coverage) | 2007 (99%) | None | None |
| ITN coverage (< 5 yrs)d | 6.5% | 5.8% | 12.8% |
| > 2 doses of IPTp at ANC visitd | 24.6% | 14.0% | 15.7% |
| Prompt treatment of fever (< 5 yrs) d | 23.8% | 22.0% | 31.7% |
| ACT coveragee | 81% | 55% | 43% |
| Outpatient level IV health facility data (UMSP data December 2009 – May 2010) | | | |
| Name of health facility | Kihihi | Walukuba | Nagongera |
| Average Number of patients per month | 2117 | 3048 | 1891 |
| Proportion with suspected malaria | 73% | 76% | 73% |
| Slide positivity rate (< 5 yrs) | 46% | 44% | 69% |
| Slide positivity rate (> 5 -15 yrs) | 44% | 48% | 48% |

a Uganda Population and Housing Census, 2002 (Ugandan Bureau of Statistics)

b Data only available from September – November 2008

d Uganda Demographic and Health Survey, 2006

e Proportion of patients with malaria prescribed an ACT at UMSP sentinel health facilities (December 2008-May 2009)

Figure 1. Study sites

**
[figure not shown]
**

##

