## 5.1 Household survey

### 5.1.1 Selection of households

A sample of 200 residential households will be selected in each site. In order to create a sampling frame for the selection of participating households, all residential households within each of the three sites have been enumerated and mapped prior to the onset of the surveys as part of a separate protocol. A random sample of households will be selected from each site using computer-generated random numbers to generate a list of households to be approached. Study personnel will conduct door-to-door recruitment to identify those households with at least one adult household resident in sequential order according to the recruitment list. Households without a child of appropriate age will be removed from the recruitment list. Residents not home during the initial contact will be re-visited on at least three other occasions before eliminating them from our sample selection process. New recruitment lists will be randomly generated for each survey using replacement.

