## 8.2 Analytical plan and sample size/power calculations

Statistical analysis will be undertaken using Stata 10 (Stata Corp., College Station, TX, USA). The prevalence of malaria infection will be based on the thin and thick blood smear readings. This procedure will enable estimation of parasite density, differentiation of Plasmodium species and identification of gametocytes. The proportion of children infected with single and multiple parasite species and the mean intensity of infection/parasite density will be calculated. Differences in proportions by age, sex and transmission setting will be assessed by logistic regression and differences in means using a Student t-test (for parametric data) and a Mann-Whitney test (for non-parametric data). Prevalence of infection and anemia, and coverage rates will be presented as frequencies with appropriate 95% binomial confidence intervals. The report and other related documents will be extensively disseminated to stakeholders. Avenues for dissemination will include publications, working papers, and atlases.

Infection. The primary metric used to measure infection for both the gold standard method (community surveys) and streamlined method (school surveys) will be the parasite rate (PR), defined as the number of positive blood smears divided by the number of smears examined. For the gold standard method, PR will be measured using the cross-sectional surveys of an estimated 300 children (200 households x 1.5 children per household) aged 6-14 years from the community surveys. For the streamlined method, PR will be estimated using cross-sectional surveys of 300 children (3 schools x 100 children per school) aged 6-14 years from the primary school surveys.

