We will test the hypothesis that estimates of PR will be similar using the two methodologies. Point estimates of PR will be calculated for each biannual survey and compared using the McNemar’s test of paired proportions. Assuming that we will have a sample size of 300 children per survey for each methodology, we will have 80% power (one-sided significance level of 0.05) to reject the alternative hypothesis that there is a difference in estimates of PR assuming that the absolute difference in PR is no greater than 10% across a range of PRs in the community surveys of 20-80%. Whether or not these analyses show any evidence of significant differences between the methods, we will explore whether there is any systematic bias in the estimate of the streamlined method compared to the gold standard method (e.g. the streamlined method consistently over- or underestimates PR). Ecological logistic regression models will be used to predict the result of the gold standard method using data from the streamlined method, allowing adjustment for bias. Final models will then be prospectively validated in independent test sets to insure their accuracy.

Mortality. The primary metric for malaria mortality will be the relative change in absolute measures of malaria mortality. For the gold standard method, the measure of malaria morality will be the number of malaria-associated deaths in children under 5 years of age per 1,000 live births. Data on malaria mortality using the gold standard method will come from the biannual community surveys and verbal autopsy. For the streamlined method, the measure of malaria morality will be the number of malaria-associated deaths in children under 5 years of age captured by our inpatient surveillance system (described in another protocol).

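### The 800 children per year behind the mortality power statement is not derived, and is hard to reconcile with the protocol's own household figures

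*Protocol*

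**What the plan says.** Section 8.2 (Mortality) compares the year-on-year change in malaria mortality between the community surveys and inpatient surveillance. The community measure is the "number of malaria-associated deaths in children under 5 years of age per 1,000 live births". The power statement begins "Assuming that we will have a sample size of 800 children per year from the community surveys" and combines this with baseline rates of 6.5, 12.9 and 19.4 per 1000 and inpatient death counts of 12, 60 and 84 for the low, medium and high transmission sites. It claims 80% power (one-sided 0.05) for differences in relative mortality of 1.30, 0.50 and 0.41. It does not show how 800 was obtained.

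Four other places bear on that number:
- Section 5.1.1: "A sample of 200 residential households will be selected in each site". Section 4.1 says the surveys run "twice a year for at least 2 years in the 3 different sites".
- Section 8.2 (Infection) shows its own multiplication for older children: "an estimated 300 children (200 households x 1.5 children per household) aged 6-14 years".
- Table 1 in section 4.2, from the 2002 census, gives for Kanungu, Jinja and Tororo in that order: "Persons per household | 4.7 | 4.5 | 4.8".
- Section 5.1.1 also requires at least one adult resident, and removes households that lack a child of an age it does not define.

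**The concern.** The 800 is the only community sample size in the mortality calculation. Multiplied by the assumed rates it gives very few expected malaria deaths, and those few deaths supply most of the variance of the comparison. If two rounds of 200 households yield clearly fewer children, the plan claims more power, and smaller detectable differences, than it has. Section 8.2 then uses this comparison, with the bias modelling, to judge whether inpatient surveillance can stand in for the community method.

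The parasite-rate paragraph of the same section writes out households times children per household. The mortality paragraph does not, so the reader has to work backwards to see what it assumes.

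**Working it through.** **1. What 800 requires.** The rates and inpatient counts are given site by site, so 800 is read as per site. The outcome is death before age five, so it is read as under-fives.
- Household visits per site per year: 2 x 200 = 400.
- Under-fives needed per household: 800 / 400 = 2.0.

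**2. Fit with the protocol's household figures.**
- Under-fives plus ages 6-14: 2.0 + 1.5 = 3.5 per household.
- Left for five-year-olds and everyone aged 15 or over: 4.5 - 3.5 = 1.0 (Jinja), 4.7 - 3.5 = 1.2 (Kanungu), 4.8 - 3.5 = 1.3 (Tororo).
- Five-year-olds at the 6-14 density: 1.5 / 9 = 0.17.
- Left for ages 15 or over: 0.83, 1.03 and 1.13. Every enrolled household must have an adult, and at Jinja the average falls below one.
- Children per year of age: 2.0 / 5 = 0.40 at 0-4 against 1.5 / 9 = 0.167 at 6-14, a ratio of 2.4.

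**3. Effect of the filter in 5.1.1.** The protocol gives no under-fives-per-household figure, so this step rests on assumptions. Take the unfiltered mean m as 1.0 to 1.5 times the 6-14 density: 5 x 0.167 = 0.83, up to 1.25. Without a filter, 400m = 333 to 500. On the most favourable reading (at least one under-five required) and with Poisson counts, the mean per recruited household is m / (1 - exp(-m)):
- m = 0.83: 1.47, or about 590 per site per year.
- m = 1.25: 1.75, or about 701.
- Reaching 800 needs m of about 1.6.

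**4. The stated power.** With Poisson deaths and the delta method, the SE of the difference between two ratios that share a true value R is

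SE = R x sqrt(1/d + 1/(R d) + 1/e + 1/(R e)),

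where d = n x rate / 1000 and e = 12, 60, 84. Power = Phi(difference / SE - 1.645).
- At n = 800, d = 5.2, 10.3, 15.5. The community part supplies (1/d) / (1/d + 1/e) = 70%, 85% and 84% of the variance.
- At R = 1, SE = 0.743, 0.477, 0.391. Power at the stated differences is then 54%, 28% and 28%. The 80% is not reproduced.
- The protocol states no true ratio. The R that gives exactly 80% at n = 800 is 0.61, 0.28 and 0.28.

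**5. Sensitivity to n, holding those R fixed** (illustration only; low / medium / high transmission site):

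| n | Expected deaths | Power | Difference detectable at 80% |
|---|---|---|---|
| 800 | 5.2 / 10.3 / 15.5 | 80 / 80 / 80% | 1.30 / 0.50 / 0.41 |
| 700 | 4.6 / 9.0 / 13.6 | 77 / 76 / 76% | 1.363 / 0.530 / 0.434 |
| 600 | 3.9 / 7.7 / 11.6 | 72 / 71 / 71% | 1.443 / 0.567 / 0.464 |
| 450 | 2.9 / 5.8 / 8.7 | 64 / 61 / 61% | 1.615 / 0.645 / 0.528 |

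**The case against.** The strongest reply is that the household ceiling may not bind.
- **The denominator is inferred.** The sentence says neither under-five nor per site. The measure is per live birth, and the women's questionnaire (5.2.4) takes birth histories that include dead and possibly non-resident children. Verbal autopsy (5.2.5) reaches back five years. Such children are not among Table 1's persons per household.
- **The subtraction mixes two bases.** Table 1 is a 2002 district average over all households, while the sites are single sub-counties and 5.1.1 drops households without a suitable child. Recruited households would be larger and have more children.
- **The power losses are not the plan's own.** They use back-solved true ratios and a delta-method variance for both arms, whereas the plan specifies a bootstrap for the community arm.
- **The stakes are limited.** The primary outcomes are parasitemia and anemia prevalence, and the substitution decision also rests on whether bias can be corrected.

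Most of this stands, and it rules out three readings that a reader might infer. The first is that the design cannot deliver 800: the filter leaves 800 strained but possible, so that is not proven. The second is that some lower figure, such as 330-450 or a ceiling of 650, is the right one: these depend on assumed numbers of adults or on carrying the 6-14 density down to ages 0-4, and the protocol states neither. The third is that the 80% is wrong even at 800: failing to reproduce it with a simple formula and an unstated true ratio is not proof of error.

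The reply does not supply support for 800. The live-birth reading leaves the denominator undefined. The favourable filter reading still falls short over the range of means tried, and sits awkwardly with section 4.1: "In the community surveys, 200 households will be recruited from a list randomly generated from a census database at each site". Redrawing lists with replacement can only reduce the number of distinct children.

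**Conclusion.** The concern holds in limited form. The 800 is an underived input to a stated 80% power. Read as under-fives per site per year, it needs 2.0 per household, leaves about 0.8-1.1 persons aged 15 or over in an average household, and implies a 2.4-fold jump in children per year of age relative to ages 6-14. These figures are arithmetic on the protocol's own numbers, with five-year-olds taken at the 6-14 density. The 590-700 yield adds two assumptions: Poisson counts and an unfiltered mean of 0.83-1.25.

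If the true number is below 800, the power for 1.30, 0.50 and 0.41 is overstated. The loss would be modest near 700 (about 3 to 4 percentage points) and substantial near 450 (about 16 to 19 points). Those sizes are conditional on the back-solved true ratios and are not estimates of the study's actual power. The matter merits correction because the plan relies on the figure and the data to settle it have already been collected.

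**What to change.** In section 8.2 (Mortality):
1. Replace 800 with an explicit product for each site: household visits per year times under-fives (or births) per household, taken from the household enumeration that 5.1.1 says is complete.
2. Say what the denominator is (resident under-fives, live births or child-years) and pair it with a rate on the same basis. If births are pooled across surveys through the five-year recall, say so.
3. Define the age in the 5.1.1 filter and reconcile it with the plain random sample of 200 households in 4.1, so that the per-household figure describes the households actually recruited.
4. Restate the expected community malaria deaths and the differences detectable with 80% power at each site, giving the assumed true ratio.

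The ranges worked out here should not be entered in the protocol as fact. The cost is one recalculation and a short rewording, with no extra recruitment. The likely downside is a less favourable stated detectable difference.
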